### Statistical aspects

The primary endpoint at the start of the study was the cumulative rate of death plus non-fatal-MI and non-fatal stroke. The expected incidence of the primary endpoint was based on the literature and on the events observed in a subgroup of patients of a previous trial conducted in a similar setting of patients and GPs (16). Overall, the rate of events included in the primary endpoint was expected to be 2% per year (10% in five years). The goodness of these sample size calculation was to be assessed after one year of follow-up and the observed rate of events was in fact much lower than expected (1.4% instead of 2%).

Because n-3 PUFA seemed to have a positive influence on various CV outcomes besides the MI and stroke, and considering the increasing burden for public health systems of CV events requiring hospitalization, time to first occurrence of CV death and hospitalization for CV reason was then established as the primary efficacy endpoint of the trial. The expected cumulative rate of these combined end points during the five-year follow-up was assumed to be 15%. The minimum clinically relevant beneficial effect of the test treatment on the cumulative endpoint is set at 15% relative risk reduction (2.25% absolute risk reduction). Accordingly, to detect the efficacy of treatment with a power of 90% and α = 0.05 at least 11,202 patients must be included with a mean follow-up of five years and ≤10% drop outs. To guarantee adequate study power, an event-driven approach was adopted and patients will be followed-up until 1,383 events occur for the primary endpoint.

Statistical differences in the baseline characteristics of the treatment groups will be assessed with the χ^2 ^test for categorical variables and *t *test for continuous variables. Treatment efficacy on the primary endpoint, and on each single component, will be assessed using a Cox's proportional hazards' model [36], and the results will be expressed as hazard ratio (HR) estimates with 95% confidence intervals (CIs). Efficacy analyses will be adjusted for covariates found to be unbalanced between randomised treatments. Kaplan-Meyer estimates of the survival curves will be presented [37]. Time of occurrence of primary combined endpoint will be calculated according to the following hierarchy: time of occurrence of cardiovascular mortality or time of first occurrence of hospitalization for CV reasons.

An interim analysis to assess the efficacy on the primary endpoint is scheduled at approximately half the expected events. This will be monitored using the sequential procedure of Peto [38] and the study will be stopped when the corresponding significance level of evidence reaches α ≤ 0.001.

All analyses will be according to the intention-to-treat approach in which all randomized patients are included, regardless of the adherence to study treatment. A per protocol analysis will be done for patients who take at least 80% of their treatment.

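### Efficacy models are to be adjusted for covariates found unbalanced between arms, which selects covariates by chance and not by prognostic strength

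*Protocol article*

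**What the plan says.** All of this is in the protocol article, Methods, Statistical aspects, unless noted.

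- Baseline comparison: "Statistical differences in the baseline characteristics of the treatment groups will be assessed with the" chi-square test for categorical variables and the t test for continuous ones.
- Primary endpoint: "time to first occurrence of CV death and hospitalization for CV reason was then established as the primary efficacy endpoint of the trial".
- Model: efficacy on the primary endpoint and on each component "will be assessed using a Cox's proportional hazards' model", reported as a hazard ratio (HR) with 95% confidence interval.
- Covariates: the next sentence reads "Efficacy analyses will be adjusted for covariates found to be unbalanced between randomised treatments".

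The article names no covariate, defines no threshold for imbalance, and does not say whether an adjusted or an unadjusted HR is primary. The primary endpoint is not exempted from the rule. Under Study procedures, treatment is allocated centrally by telephone from a computer-generated list stratified by GP. The model description does not mention that stratification.

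**The concern.** With central randomisation, a difference between arms at baseline is due to chance, so a significance test of it examines a null hypothesis already known to be true. A covariate earns its place in an efficacy model by predicting the outcome, and the size of its chance imbalance says nothing about that. Under the stated rule, a variable with no bearing on cardiovascular events is as likely to enter as age, previous cardiovascular disease or diabetes.

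Two things are at stake. First, the efficacy model cannot be specified until baseline data have been compared by arm. Second, the precision available from known prognostic factors is mostly forgone. Because the rule is stated outright, this is a method that has been fixed badly. It is not a detail left to an analysis plan that we have not seen.

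**Working it through.** **1. The plan's own figures.** The assumptions are 15% against 12.75% at five years, 90% power, alpha 0.05 (taken as two-sided), at most 10% dropout, and 1:1 allocation (not stated).

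- Two proportions with continuity correction: 5,047 per arm, 10,094 in total; 10,094 / 0.9 = 11,216, against the stated 11,202.
- Implied HR = ln(1 − 0.1275) / ln(1 − 0.15) = 0.839. Schoenfeld: 4 × (1.960 + 1.282)² / (ln 0.839)² ≈ 1,369 events; Freedman: 1,376. The plan states 1,383.

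Both figures are reproduced to about 1% or better without any allowance for covariates. The design therefore does not depend on adjustment, and changing the covariate rule leaves both figures as they are.

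**2. How often the rule selects something.** Table 1 lists 30 characteristics: age, sex and previous cardiovascular disease (3), risk factors (8), measurements (10) and drug classes (9). The article does not say which will be tested. Assume a 5% two-sided threshold and K independent tests, so that P(at least one selected) = 1 − 0.95^K.

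| K | Expected number selected | P(at least one) |
|---|---|---|
| 10 | 0.5 | 40% |
| 20 | 1.0 | 64% |
| 25 | 1.25 | 72% |
| 30 | 1.5 | 79% |

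Any one named factor is selected with probability 5% and omitted with probability 95%, however prognostic it is.

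**3. What this does to inference.** The simulation used 12,512 patients, 25 independent candidate covariates of which 5 are prognostic, an exponential proportional-hazards model and 1,500 replicates. Each simulated trial was analysed in three ways. The prognostic strengths are assumptions, and the event count was not tied to 1,383, so compare within rows and do not read the levels as the trial's power.

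| Log-HR per SD of each prognostic factor | Quantity | Unadjusted | Imbalance rule | Prespecified five |
|---|---|---|---|---|
| 0.2 | Type I error | 4.2% | 4.3% | 4.7% |
| 0.4 | Type I error | 5.3% | 4.9% | 5.4% |
| 0.2 | Power, HR 0.85 | 83.4% | 83.1% | 84.1% |
| 0.4 | Power, HR 0.85 | 78.5% | 79.3% | 83.8% |

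The Monte Carlo error of each power figure is about 1 point: √(0.83 × 0.17 / 1,500) = 0.0097. At least one covariate was selected in 70% to 74% of replicates, in line with the 72% from the formula at K = 25.

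**4. The power gap in events.** The required number of events is proportional to (1.960 + z_power)².

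- Weaker factors: (1.960 + 0.999)² / (1.960 + 0.958)² = (2.959 / 2.918)² ≈ 1.03.
- Stronger factors: (1.960 + 0.986)² / (1.960 + 0.817)² = (2.946 / 2.777)² ≈ 1.13.

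Prespecification is thus worth about 3% to 13% in events compared with the imbalance rule.

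**5. The quantity estimated.** With strength 0.4, the mean log-HRs were −0.1556 (unadjusted), −0.1559 (imbalance rule) and −0.1643 (prespecified), that is, HRs of 0.856, 0.856 and 0.848. With strength 0.2 they were −0.1602, −0.1604 and −0.1625, or 0.852, 0.852 and 0.850. The HR adjusted for the prognostic set is conditional on it and lies slightly further from 1.

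**The case against.** The best defence is that the rule does little damage. Selection uses baseline data and not outcomes, so a covariate set could be settled before outcomes are examined by arm. Type I error is not inflated, and the average estimate under the rule is almost the same as the unadjusted one. The sample size makes no allowance for covariate gain, so unused precision is a missed improvement and not a shortfall in planned power. All of this stands.

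Some stronger readings are tempting, but the document does not support them:

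- **The test or its standard error is invalid.** A reader might infer this because selection precedes fitting. At 4.3% to 4.9%, the simulated type I error gives no sign of it.
- **The adjusted HR is declared primary.** The article speaks of efficacy analyses in general and does not label the adjusted result as primary. It does not exempt the primary endpoint either.
- **Imbalance means p < 0.05.** This is an assumption. The testing and adjustment sentences are separate, and a threshold and candidate list could properly sit in the analysis plan.
- **About four trials in five will pick up a chance covariate.** The 79% needs all 30 items of Table 1 tested independently. Many are plainly related: BMI and obesity, total and LDL cholesterol, blood pressure and hypertension, diabetes and glucose or its drugs.

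What survives is the principle. No threshold or candidate list turns chance imbalance into a measure of prognostic value.

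**Conclusion.** The point holds as a moderate weakness that should be fixed; it does not threaten the validity of the trial. The stated rule chooses covariates by chance. It leaves the efficacy model undetermined until baseline data are compared by arm, and it recovers little or none of the precision that prognostic covariates offer. The loss is about 1 to 4.5 points of power, or 3% to 13% in events. The lower end is no larger than the simulation error, and where the trial falls in that range depends on prognostic strengths that the document does not give. The 40% to 79% selection range rests on an assumed 5% threshold, 10 to 30 tests, and independence between them.

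**What to change.** Replace the adjustment sentence, before unblinding, with the following:

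1. A short list of prognostic covariates, used whatever the observed balance, for example age, sex, previous atherosclerotic cardiovascular disease, diabetes and smoking.
2. A statement of whether the adjusted or the unadjusted HR is primary, with the other reported as a sensitivity analysis.
3. A statement of how the stratification of randomisation by GP is handled in the model.
4. Baseline comparisons between arms used for description only, and not to select covariates.

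The cost is a change of wording. The article describes the study as ongoing, and the covariates suggested are already recorded at enrolment. The sample size and the 1,383-event target stay as they are. One small downside should be acknowledged in the plan: the adjusted HR is conditional on the covariates and will differ slightly from the unadjusted HR, so the plan should say which of the two the trial's conclusion rests on.

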### Ethical/regulatory aspects

The ethical conduct of the study is regulated by the last revision of the Helsinki Declaration. The study is consistent with Good Clinical Practice (GCP) principles and procedures, as described in the ICH Harmonized Tripartite Guideline for Good Clinical Practice (1996); Directive 93/39/CEE The Rules Governing Medicinal Products in the European Community. The study complies with Italian law, Directive 10 May 2001, "Controlled Clinical Trials in the Setting of General Practice and Pediatrics".

The study protocol was approved by the Italian health authorities, the Ethics Committee of the Chairman's Institution and by the local Ethics Committees. An *ad hoc *insurance policy was stipulated for patients and GPs.

This study is registered in a public clinical trial database (ClinicalTrials.gov NCT00317707).

### Trial update

A total of 1,620 GPs attended 34 local training meetings organized throughout Italy; 860 (58%) out of 1486 GPs who initially agreed to join the study started to recruit patients (Figure 2). Between February 2004 and March 2007, 12,513 patients were enrolled. Each GP admitted an average of 14 patients (range 1-79); respectively 271 (31.5%), 564 (65.6%), and 25 (2.9%) GPs recruited ≤10, 11-20, and more than 20 patients.

**Figure 2 F2:**
[figure not shown]
**Rischio & Prevenzione research network**. Red circle = Local health units in the Italian regions participating in the study. The nation-wide research network comprised 860 general practitioners in 57 local health units, who admitted 12,513 patients to the study.

The main inclusion criterion was diabetes mellitus plus one or more CV risk factors (46.9%). About 30% of patients were admitted because of clinical evidence of atherosclerotic CV, except a history of MI: angina pectoris (12.0%), revascularization procedures (8.8%), peripheral artery disease (7.8%), previous transient ischemic attack (8.1%) or ischemic stroke (4.0%). Multiple CV risk factors (≥4 risk factors, except diabetes mellitus) were the inclusion criterion for 21.1% of patients. Less than 1% were included for other reasons. The main baseline features of the study population are shown in Table 1.

**Table 1 T1:** Baseline characteristics of Risk & Prevention participants

	**% or mean (SD)**
	
*Age (years)*	
Mean	63.9 (9.5)
≤50	7.4
51-59	22.9
60-69	39.6
70-79	27.0
≥80	3.0
	
*Males*	61.5
	
*Previous CVD*	29.6
	
*Cardiovascular risk factors*	
Hypertension	84.6
Hypercholesterolemia	71.1
Diabetes mellitus	59.9
Obesity	48.6
Family history of premature CVD	31.1
Cigarette smokers	21.7
Unhealthy diet	63.9
Physical inactivity	56.1
BMI (kg/m2)	29.3 (4.9)
SBP (mmHg)	140.2 (15.2)
DBP (mmHg)	82.7 (8.2)
Heart rate (bpm)	74.4 (8.4)
Total cholesterol (mg/dL)	215.9 (42.6)
LDL cholesterol (mg/dL)	132.1 (36.4)
HDL cholesterol (mg/dL)	51.1 (13.3)
Triglycerides (mg/dL)	168.7 (99.8)
Fasting blood glucose (mg/dL)	132.8 (46.7)
* HbA1C (%)	7.0 (1.5)
	
*Medical treatment*	
ACE inhibitors	45.1
ARBs	21.9
Diuretics	41.5
Calcium - channel blockers	28.2
β-blockers	20.6
Oral hypoglycemic drugs	44.1
Insulin	6.6
Statins	41.1
Antiplatelet agents	41.4

*in diabetic patients

CVD, cardiovascular disease; BMI, body mass index; SBP, systolic blood pressure; DBP, diastolic blood pressure; LDL, low-density lipoprotein, HDL, high-density lipoprotein, HbA1C, glycated hemoglobin, ACE, angiotensin-converting enzyme; ARB, angiotensin receptor blocker

## Discussion

As shown in Figure 2 and Table 1, the first and certainly one of the most important results of the study is that it proved feasible to create a network of collaborating physicians to generate a prospective cohort adequately representative of practice throughout the country. The GPs' participation is mainly motivated by the acknowledgment that the study is an expression of the duty to continuous professional education. It is also a reminder of the close links between research and practice: the only way to be informed and responsible about whatever is uncertain or unknown, is to investigate it through a research protocol.

The protocol therefore - as a general design, but even more as an operational trial - is the product of a truly collective interplay among dozens of colleagues, and it was open to discussion at the 34 presentations organized throughout the country. One of the GCP requirements - continued education meetings for investigators to verify quality and surveillance of data collection - has been used as an opportunity for sharing and optimizing a project, more than just a teaching exercise on the technicalities of trial procedures.

Consistently with this approach, the inclusion criteria in the trial are not just a list of "objective" data: they mimic the process of an informed decision, which is a mix of documented knowledge, of "perceived" overall clinical condition of risk, and a judgment of opportunity. The epidemiological variability of the study population is not only expected (as explicitly set out in the protocol), but needed, to ensure the population is really representative, and therefore the descriptive and experimental results once they become available can be transferred appropriately.

The patients'actual level of CV risk is lower than expected. However, this is not surprising: beside the fact that the cohort is younger than expected, current patients are more widely exposed to preventive measures. In fact, the rate of events reported in previous or observational studies reflects clinical practice at that time and overestimates the current risk.

The decision to modify the study endpoint fits well with the public health-oriented design of this GP based project and shows that a trial is simply one part of a strategy of comprehensive prospective monitoring and assessment of all those patients deemed to be at a specific risk. Their epidemiological outcomes over the medium-long term provide the most important knowledge from which to interpret the experimental results, which will show whether or not the "new" treatment adds a specific advantage to the "natural" history of this population (i.e. under the GPs' routine care).

Finally, the scientific interest and "modernity" of the experimental hypothesis tested in R&P is confirmed by the GISSI-HF trial results which further support the benefit of n-3 PUFA on mortality seen in GISSI-Prevenzione [17], confirming a significant reduction of deaths in patients with heart failure [39]. Similarly, the benefit of n-3 PUFA in Japanese people suggests that it might be replicated in other populations, and might be even more substantial with higher levels of intake [40]. Novel results like this in the field of cardiology fuel the hypothesis of anti-arrhythmic and anti-atherosclerotic effects of n-3 PUFA and show how important it is to testing their efficacy in a GP's population of patients at high CV risk.

## Abbreviations

CHD: Coronary Heart Disease; CIs: Confidence Intervals; CVD: Cardiovascular Disease; CV: Cardiovascular; DHA: Docosahexanoic acid; DSMB: Data Safety Monitoring Board; EPA: Eicosapentaenoic acid; GCP: Good Clinical Practice; GISSI-HF: Gruppo Italiano per lo Studio della Sopravvivenza nell'Infarto miocardico - Heart Failure; GISSI-Prevenzione: Gruppo Italiano per lo Studio della Sopravvivenza nell'Infarto miocardico-Prevenzione; GP: General Practitioner; HR: Hazard Ratio; MI: Myocardial Infarction; N-3 PUFA: n-3 polyunsaturated fatty acids; RCTs: Randomized Controlled Trials; R & P: Rischio & Prevenzione.
